### Sample size calculation

In the present study, we expected a 60% PR from the augmented group and up to a 30% PR from the limited group. These anticipated percentages were derived from previous studies [9, 14], and a consensus of experts in clinical gastroenterology. Significance was determined as α = 0.05, and a power of 1 – β = 0.80 was used. Accordingly, the required sample size in this trial was estimated according to the following formula where (p_a_ + p_l_)/2:$$ n=\frac{{\left({\mathrm{Z}}_{\upalpha /2}\sqrt{2\overline{p}\left(12\overline{p}\right)}+ Z\beta \sqrt{p_a\left(1-{p}_a\right)+{p}_l\left(1-{p}_l\right)}\right)}^2}{{\left({p}_a-{p}_l\right)}^2} $$

Assuming p_a_ = 0.6 (p_a_: the effect on the augmented group) and p_l_ = 0.3 (p_l_: the effect on the limited group), a sample size of *n* = 40 is calculated to achieve 5% significance level and 80% power. Assuming a dropout rate of 10%, a total of 88 participants were needed with a 1:1 allocation to each group (44 participants per group).

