### Statistical analysis

To compare demographic or clinical characteristics a two-sample *t*-test (in case of continuous data) or Chi-square test (in case of binary data) will be used. If a significant difference is identified between the augmented and limited groups, a general linear model-analysis of covariance will be used for continuous data, and logistic regression analysis will be used for binary data. To compare the mean value of two groups, a two-sample *t*-test will be used as a parametric method, and Mann-Whitney test will be used as a non-parametric method. The paired *t*-test will be used as parametric method and Wilcoxon signed ranks test will be used as non-parametric method to compare variables before and after intervention. The repeated measured *t*-test will be used to compare the mean value of variables between the two groups. A *P* value of <0.05 will be considered as statistical significance. Efficacy will be investigated as the difference between baseline (1 week) and the completion of treatment (4 weeks). To assess the efficacy of interventions, both intention to treat and per-protocol analysis will be performed. Participants who complete the clinical trial without any violations are targeted in per-protocol analysis. Statistical analysis other than described above will follow Guideline for Clinical Trial Statistics (Article No. 65615–13,553, December 29th 2000).

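### The printed sample-size formula gives 42 per arm rather than 40, and the 10% dropout allowance is one patient per arm short; power with 10% lost is about 78%, not 80% (minor)

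*Protocol article*

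**What the plan says.** The section Sample size calculation gives every input. For the responder rates, "we expected a 60% PR from the augmented group and up to a 30% PR from the limited group". For the error rates, "Significance was determined as α = 0.05, and a power of 1 – β = 0.80 was used". The formula uses Z at alpha/2, so the test is two-sided. The section says that "the required sample size in this trial was estimated according to the following formula" and displays the version with a pooled-variance term under the null hypothesis and separate variances under the alternative. It then reports that "a sample size of *n* = 40 is calculated to achieve 5% significance level and 80% power", and finishes with the dropout step: "Assuming a dropout rate of 10%, a total of 88 participants were needed with a 1:1 allocation to each group (44 participants per group".

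The section Statistical analysis adds that "both intention to treat and per-protocol analysis will be performed".

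**The concern.** Formula, inputs and answer stand together in one section, so a reader can check them directly, and they do not agree. The dropout step does not return the number it is meant to protect. Both slips lower the total.

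This section is the only justification given for 88 patients. If the trial finds no significant difference, that result will be read against the stated 80% power. The figure should therefore follow from the formula and dropout rate printed beside it.

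**Working it through.** **Inputs (all from Sample size calculation).** p_a = 0.60, p_l = 0.30, difference 0.30, mean p̄ = 0.45; two-sided alpha 0.05 (Z = 1.960); power 0.80 (Z = 0.8416); dropout 10%; 44 per arm, 88 in total.

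**One reading to declare.** In the text at hand the formula shows 12p̄ where 1 - p̄ belongs, and the definition of p̄ has lost its left-hand side. I read both as typesetting or extraction faults and do not count them as errors. Taken literally, 12p̄ would give about 265 per arm; 1 - 2p̄ would give about 15. Neither can be meant.

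**Step 1. Reproduce the stated 40.** The unpooled-variance formula gives

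n = (1.960 + 0.8416)² x (0.6 x 0.4 + 0.3 x 0.7) / 0.30² = 7.849 x 0.45 / 0.09 = 39.24, so 40 per arm.

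This matches the stated figure, but it is not the formula printed.

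**Step 2. Apply the printed formula.**

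n = (1.960 x √(2 x 0.45 x 0.55) + 0.8416 x √(0.24 + 0.21))² / 0.30² = (1.3790 + 0.5646)² / 0.09 = 41.97, so 42 per arm.

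Other common variants do not give 40 either: arcsine 41.8 (42), pooled variance in both terms 43.2 (44), continuity-corrected 49, one-sided 33.

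**Step 3. Dropout.**
- As done: 40 x 1.10 = 44 per arm, 88 in total.
- Left after 10% loss: 44 x 0.90 = 39.6 per arm.
- Required from 40: 40 / 0.90 = 44.4, so 45 per arm, 90 in total.
- Required from 42: 42 / 0.90 = 46.7, so 47 per arm, 94 in total.

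**Step 4. Power delivered by 44 per arm, at 60% versus 30%.**

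| Analysed per arm | Printed formula | Unpooled formula | Exact, uncorrected chi-square |
|---|---|---|---|
| 39.6 (10% lost) | 77.6% | 80.4% | 78.0% at 39/39; 76.1% at 39/40 |
| 40 | 78.0% | 80.7% | 79.6% |
| 42 | 80.0% | 82.6% | 82.8% |
| 44 (all 88) | 81.9% | 84.3% | 81.1% |

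The exact figures do not rise smoothly with n because the outcome counts are discrete.

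**Step 5. A sensitivity figure, on an assumption the article does not state.** Suppose the 10% who drop out stay in the intention-to-treat set and all count as non-responders. The rates become 0.9 x 0.60 = 0.54 and 0.9 x 0.30 = 0.27. At 44 per arm the printed formula then gives

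Z = (0.27 x √44 - 1.960 x √(2 x 0.405 x 0.595)) / √(0.54 x 0.46 + 0.27 x 0.73) = (1.791 - 1.361) / 0.667 = 0.645, a power of 74.0%.

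**The case against.** The strongest reply is that 40 is a legitimate answer from a standard method and the section merely displays the wrong variant beside it. On that view the whole matter is a citation mismatch plus one patient per arm in the dropout step (88 against 90). With the unpooled formula, the 39.6 per arm left after dropout still have 80.4% power. A difference of about 2 points is also small beside the uncertainty in the 60% and 30%, which the article bases on earlier studies and expert consensus. All of this stands, and it is why the point is minor. It does not make the section correct, since the printed formula and its printed result still disagree. The exact chi-square figures at 39 to 40 per arm also fall a little short of 80%.

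A reader might go further and infer that 88 patients cannot deliver 80% power. The document does not support that without a condition. An intention-to-treat analysis is planned, and if all 88 contribute at the assumed rates the printed formula gives 81.9% and the exact chi-square 81.1%. The shortfall needs 10% to leave the analysis, or to stay in it with diluted response.

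Lower figures are also tempting. Fisher's exact test would give 70.3% at 39/39 and 72.5% at 40/40, but the article does not name that test; the only binary test it names is the chi-square, in the sentence on demographic or clinical characteristics. The 74% in Step 5 needs a missing-data rule that the article does not state and that a statistical analysis plan would commonly hold. Neither figure can be imposed as the trial's power.

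**Conclusion.** Wrong as written, and minor. Two statements fail on the section's own terms: the printed formula yields 42 per arm rather than 40, and adding 10% to 40 does not leave 40 after a 10% loss. By the printed formula the cost is about 2.4 points of power when 10% are lost (77.6% against 80%). There is no shortfall when all 88 are analysed at the assumed rates.

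The conclusion rests on the article's rates, its two-sided alpha, and reading the damaged term as 1 - p̄. The validity of the comparison is unaffected. The larger total of 94 is what the printed formula requires; it is not the only total these inputs can justify, since starting from 40 per arm gives 90.

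**What to change.** Correct the paragraph and keep 88:

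- Either print the unpooled formula that gave 40, or keep the printed formula and state 42 per arm.
- Describe the dropout allowance as n/(1 - d) and say that 44 randomised per arm leaves about 39.6 after 10% loss.
- Restate the power as about 78% with 10% lost and about 82% if all 88 are analysed at the assumed rates. If the unpooled formula is printed, its own 80.4% and 84.3% can be shown beside these, but the exact chi-square figures lie closer to 78% and 82%.
- Optionally, give the 74% as a sensitivity figure, labelled with its assumption that dropouts count as non-responders.

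This costs a change of wording and a slightly less favourable power figure. Recruitment has begun and the site targets (29, 30 and 29) already add up to 88; nothing in the design, allocation or conduct has to change. If the sponsor wants 80% power after 10% loss, the consistent total is 94 by the printed formula, or 90 from 40 per arm.

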### Statistical analysis

To compare demographic or clinical characteristics a two-sample *t*-test (in case of continuous data) or Chi-square test (in case of binary data) will be used. If a significant difference is identified between the augmented and limited groups, a general linear model-analysis of covariance will be used for continuous data, and logistic regression analysis will be used for binary data. To compare the mean value of two groups, a two-sample *t*-test will be used as a parametric method, and Mann-Whitney test will be used as a non-parametric method. The paired *t*-test will be used as parametric method and Wilcoxon signed ranks test will be used as non-parametric method to compare variables before and after intervention. The repeated measured *t*-test will be used to compare the mean value of variables between the two groups. A *P* value of <0.05 will be considered as statistical significance. Efficacy will be investigated as the difference between baseline (1 week) and the completion of treatment (4 weeks). To assess the efficacy of interventions, both intention to treat and per-protocol analysis will be performed. Participants who complete the clinical trial without any violations are targeted in per-protocol analysis. Statistical analysis other than described above will follow Guideline for Clinical Trial Statistics (Article No. 65615–13,553, December 29th 2000).

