### Randomization, allocation concealment, and blinding

After participants have completed a baseline evaluation, they will be randomized to two groups: the augmented group and the limited group. The randomization will be carried out using random number lists, created in accordance with the PROC PLAN of SAS 9.4 (SAS Institute Inc., Cary, NC, USA) by an independent statistician. The acupuncture practitioner will be unaware of the allocation until opening an opaque, sealed envelope. Participants will not be informed that we are studying the patient-practitioner interaction. They will be told the study is "Acupuncture for the treatment of functional dyspepsia: An international multicenter trial." Participants will be informed of the purpose of the study in a debriefing session at the end of the study. The Clinical Research Coordinator evaluating the variables will be blinded to the allocation.

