#### Treatment fidelity

In order to evaluate compliance with the protocol and treatment fidelity, the first acupuncture session for all subjects will be videotaped. Ten percent (10%) of videotapes will be randomly reviewed to assure that the practitioners in the augmented and limited groups follow the standard operating procedure. Patients will be made aware of the recording as part of the informed consent process, and only the interview will be recorded. Participants will be told that the purpose of the recording is to assure practitioners compliance with the protocol. Videotaping of treatment will not be performed, and the practitioner will assure that the video is turned off when the acupuncture treatment starts.

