### Quality control

To confirm the quality of the study, all practitioners of acupuncture will be required to have a license and more than 2 years of experience. To improve consistency, all researchers will be trained several times in both the augmented and limited context. Outcome measurements are retained in the source documents, the hospital or private records, and the laboratory results and records. Original data in source documents will be recorded into the electronic Case Report Form (e-CRF). The data entered into the e-CRF will be identical to the original data. Independent investigators and the Clinical Research Coordinator will verify the accuracy of the data in the e-CRF, and an independent statistician will analyze the data. If participants do not complete the study, the reasons will be fully documented.

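### Practitioners deliver the whole randomised contrast, but no listed test includes practitioner and the text leaves open whether each one treats both arms

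*Protocol article*

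**What the plan says.** Under Acupuncture treatment, the protocol article has needling done identically in both groups. The arms differ only in how the practitioner behaves (Augmented group, Limited group, Table 1). Background and Discussion frame the aim as the influence of the patient-practitioner relationship in general.

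Statistical analysis lists these methods:
- For demographic or clinical characteristics, a two-sample t-test for continuous data or, for binary data, "Chi-square test (in case of binary data) will be used".
- ANCOVA or logistic regression, only if the groups differ significantly.
- For two means, a two-sample t-test, or "Mann-Whitney test will be used as a non-parametric method".
- Paired tests within group, and a repeated-measures t-test between groups.

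No method names practitioner, and no test is explicitly assigned to the responder proportion.

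Three places bear on who treats whom:
- Randomization, allocation concealment, and blinding: "The acupuncture practitioner will be unaware of the allocation until opening an opaque, sealed envelope".
- Quality control: "all researchers will be trained several times in both the augmented and limited context".
- Treatment fidelity: videotapes are reviewed to check that "the practitioners in the augmented and limited groups follow the standard operating procedure".

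The number of practitioners is not given. The Sample size calculation has no allowance for practitioner.

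**The concern.** When the treatment is a style of behaviour, the person delivering it is part of the treatment. Two things can then go wrong with tests that see only patients and arms.

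- **Nested practitioners.** If different people deliver the two styles, the arm difference is partly a difference between individuals, and randomising patients does not remove it.
- **Crossed practitioners with a varying effect.** If each person delivers both styles but some perform the contrast better than others, the arm effect varies by practitioner. That variation matters for a general statement about the interaction, but it is absent from the error term.

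In either case a positive result that depends mainly on one practitioner would not be visible in the listed analyses. The sponsor itself treats delivery as something to control: practitioners are trained for consistency, and 10% of the first-session recordings are reviewed.

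**Working it through.** **1. The plan's own figure.** Inputs from Sample size calculation: "Significance was determined as α = 0.05", used two-sided in the printed formula; power 0.80; "we expected a 60% PR from the augmented group and up to a 30% PR from the limited group".
- Unpooled variance: (1.960 + 0.842)² × (0.24 + 0.21) / 0.09 = 39.2, so 40 per arm, as stated. The pooled form that the article prints gives 42.
- Dropout: 40 × 1.1 × 2 = 88, as stated.

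So 88 is a figure for independent patients, with a design effect of 1.

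**2. Crossed or nested.** A practitioner who learns the arm only on opening the envelope must be ready to deliver either style, and training in both contexts fits that. Both passages point to crossed practitioners. The Treatment fidelity phrase can mean one set of people per arm, or whoever is delivering either format. No sentence settles it.

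**3. Formula.** Let m be patients per practitioner per arm, b the share of outcome variance from practitioner main effects, and i the share from arm-specific practitioner effects.
- Crossed: DE = (1 − b − i) + m·i. With b = 0 this is 1 + (m − 1)·i.
- Nested: DE = 1 + (m − 1)·ICC, which is the same expression.
- Actual error of a nominal 5% test: 2 × [1 − Φ(1.96/√DE)].

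**4. Crossed, main effects only.** With b = 0.05 and i = 0, DE = 0.95 and the error is 4.4%. Simulation of this case gave 4.5-5.3%. Ignoring practitioner does no harm here.

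**5. Nested, or crossed with a varying effect.** Neither the number of practitioners nor the variance share is in the document, so both are assumed. At 44 per arm:

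| Practitioners delivering each arm | m | Share | DE | Actual error |
|---|---|---|---|---|
| 3 | 14.7 | 0.02 | 1.27 | 8.2% |
| 3 | 14.7 | 0.05 | 1.68 | 13.1% |
| 3 | 14.7 | 0.10 | 2.37 | 20.3% |
| 6 | 7.3 | 0.02 | 1.13 | 6.5% |
| 6 | 7.3 | 0.05 | 1.32 | 8.8% |
| 6 | 7.3 | 0.10 | 1.63 | 12.5% |

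A beta-binomial simulation at 40 per arm (40,000 runs, common rate 0.45) gave 8.5 / 13.5 / 20.4% with 3 and 6.9 / 9.1 / 12.4% with 6.

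**6. Does stratifying cure it?** Only for main effects. In a logit-scale simulation at 42 per arm with 3 crossed practitioners and latent shares of 0.02 / 0.05 / 0.10, the unstratified chi-square test had error 9.3 / 13.1 / 18.7%. Cochran-Mantel-Haenszel by practitioner had 7.9 / 11.8 / 17.8%. About one point of the unstratified excess is discreteness, since that test runs near 6% with no practitioner variance at all.

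**7. What a practitioner-level test can do.** Take a t-test on the per-practitioner differences, at 42 per arm, 60% v 30% and no practitioner variance. The noncentrality is 0.30 / √(0.45/42) = 2.90. The critical value is 4.30 on 2 df (3 practitioners) and 2.57 on 5 df (6). Power is about 37% and 64%.

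**The case against.** **A reader might infer that the planned error bars fail outright.** The document does not support that. Patients are randomised individually, and the envelope and training passages point to crossed practitioners, where main effects cancel. The nested reading rests on one loose phrase. That objection stands, so the point is conditional.

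**In a crossed design, the inflated error does not apply to the null that style affects nobody.** Under that null no practitioner has an arm effect, and the test holds its level. The 8-20% arises only if style helps with some practitioners, harms with others and averages zero. This also stands: for crossed practitioners the figures concern generalising to practitioners at large. For nested practitioners they do not depend on that argument.

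**The size is assumed.** True. Few practitioners is itself an inference, and scripted behaviour, 10 hours of training and video review may keep the variance share small.

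**The chi-square sentence concerns patient characteristics.** Correct. It cannot be presented as the stated primary test. But it and the conditional logistic regression are the only binary methods listed, and neither has a practitioner term.

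**Model terms and e-CRF fields belong in a SAP that is not shown.** This holds in part, and practitioner may already be recorded. But the article does name its tests, and refers to a guideline only what it has not described. The ambiguity about who treats whom lies in the protocol text itself.

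**Conclusion.** The point holds in conditional form. It is certain that practitioner behaviour is the whole randomised contrast, that no listed method includes practitioner, and that the text does not say outright whether each practitioner treats both arms. If they do and the effect is uniform, the planned comparison is sound, with error of about 4.4-5%. If practitioners are nested in arm, or the effect varies between them, precision is overstated for any conclusion beyond the participating practitioners. The figures of about 8-20% with 3 practitioners and 6.5-12.5% with 6 are illustrations that rest on an assumed practitioner number and an assumed share of 0.02-0.10; they are not estimates for this trial. This is an inexpensive improvement worth making, not a flaw that invalidates the trial.

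**What to change.** 1. In Treatment fidelity and Quality control, state how many practitioners there are and that every one treats both arms, so that these sections agree with the randomisation section.
2. Record the practitioner for each session in the e-CRF, if this is not already done. Recruitment has begun, so earlier sessions may have to be filled in from treatment records.
3. Name the primary test for the responder proportion: Cochran-Mantel-Haenszel stratified by practitioner, or logistic regression with practitioner as a factor. This also absorbs site if each practitioner works at one site. Include practitioner in the models for continuous outcomes. The purpose is precision and protection against main effects.
4. Report the arm effect for each practitioner.
5. Pre-state one sensitivity analysis that tests the arm effect against its between-practitioner variation (a random arm slope or a practitioner-level summary test), because stratification alone does not capture that variation.
6. Word the main conclusion as applying to the participating practitioners.

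**Cost.** Protocol or SAP wording and at most one data field; no extra patients or staff. The downside is that the sensitivity analysis has few degrees of freedom: power for 60% v 30% is about 37% with 3 practitioners and 64% with 6, even with no practitioner variance. It should therefore be supportive only, and a non-significant result there should not be read as contradicting the primary analysis.

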### Participants

A total of 88 patients will be recruited from three centers (Kyung Hee University Hospital at Gangdong, 29 patients; Kyung Hee University Medical Center, 30 patients; and Massachusetts General Hospital, 29 patients).

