### Outcome measurements

#### Primary outcome

##### Proportion of responder

Proportion of responder (PR) will be used to evaluate the proportion of patients who showed alleviation of FD symptoms, with relief of stomach pain or discomfort. PR is defined as the proportion of participants who answer “yes” to the adequate relief question more than half the time during the treatment period. The adequate relief question is, "After the last visit, have you had adequate relief of your stomach pain or discomfort?" The adequate relief question will be asked at every visit, starting with the second visit. PR will be calculated for the 4-week period. This indicator has been applied in several studies with functional intestinal diseases [9, 13, 14].

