#### Participant timeline

The time schedule of enrollment, intervention, and assessments is summarized in Table 3.

**Table 3 Tab3:** The schedule of enrollment, intervention, and assessments

Study period	Screening Visit	Acupuncture treatment period							
Visit		v1	v2	v3	v4	v5	v6	v7	v8
Week		1	1	2	2	3	3	4	4
Patients									
Informed Consent	√								
Demographics	√								
Physical examination	√								
History Examination	√								
Dyspepsia History Examination	√								
Inclusion/Exclusion Criteria	√								
Serologic test/ Evaluation	√								
BDI	√								
Randomization	√								
Trial evaluation									
Investigation of Concomitant medication		√^*^	√^*^	√^*^	√^*^	√^*^	√^*^	√^*^	√^*^
Adverse events		√^*^	√^*^	√^*^	√^*^	√^*^	√^*^	√^*^	√^*^
Outcomes									
AR of abdominal pain & discomfort			√^*^	√^*^	√^*^	√^*^	√^*^	√^*^	√^*^
VAS for dyspepsia	√	√^*^							√^†^
Expectations for Relief Scale		√^*^			√^*^				√^*^
MASS		√^†^	√^†^	√^†^	√^†^	√^†^	√^†^	√^†^	√^†^
The CARE measure		√^†^							√^†^
IRI		√^†^							√^†^
NDI		√^*^							√^†^
SF-36		√^*^							√^†^
STAI		√^*^							√^†^
PRISM		√^*^							√^†^
Nutrition drink test		√^*^							√^†^
Intervention									
Acupuncture treatment		√	√	√	√	√	√	√	√

^*^, conducted before acupuncture treatment; ^†^, conducted after acupuncture treatment; BDI, Beck Depression Inventory; *AR* Adequate Relief, *VAS* Visual analog scale, *MASS* Massachusetts General Hospital Acupuncture Sensation Scale, *CARE* Consultation and Relational Empathy, *IRI* Interpersonal Reactivty Index, *NDI* Nepean Dyspepsia Index, *SF-36* Short Form 36-item Health Survey, *STAI* State-Trait Anxiety Inventory, *PRISM* Pictorial Representation of Illness and Self Measure

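### Covariate adjustment depends on a significant baseline difference, so a chance-driven pre-test picks the model; the cost is power on the continuous secondary outcomes and an unfixed primary comparison (should fix)

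*Protocol article*

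**What the plan says.** All of the rule stands in the Statistical analysis section of the protocol article.

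- **Baseline test.** "To compare demographic or clinical characteristics a two-sample *t*-test (in case of continuous data) or Chi-square test (in case of binary data) will be used".
- **Trigger.** "If a significant difference is identified between the augmented and limited groups, a general linear model-analysis of covariance will be used for continuous data", and under the same condition "logistic regression analysis will be used for binary data". Because this follows directly on the comparison of characteristics, the difference meant is a baseline difference. No covariates are named.
- **Default.** "To compare the mean value of two groups, a two-sample *t*-test will be used as a parametric method", with Mann-Whitney as the non-parametric alternative. The section also says: "Efficacy will be investigated as the difference between baseline (1 week) and the completion of treatment (4 weeks", which points to change scores. It does not settle whether the between-group test uses the change or the final value.

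The primary outcome is a binary responder status. Under Proportion of responder: "The adequate relief question will be asked at every visit, starting with the second visit", so it has no baseline value. In Table 3 (Participant timeline), VAS, NDI, SF-36, STAI, PRISM and the nutrient drink test are all measured at v1 before acupuncture and again at v8. Under Participants: "A total of 88 patients will be recruited from three centers", two in Korea and one in the USA. No stated analysis includes site.

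**The concern.** In a randomized trial a baseline P value measures only chance. It does not show whether the variable predicts the outcome, which is what makes adjustment worthwhile. Three consequences follow.

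- A covariate that predicts the outcome is left out of the model in about 95% of trials, and the precision it would give is lost.
- An imbalance just short of significance goes uncorrected, or is over-corrected by a change score.
- The model is known only after the data are seen. For binary data the switch also changes what is estimated, from a marginal comparison of proportions to a conditional odds ratio.

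The rule is written into the article, so this is not a detail left to an analysis plan. An unseen plan could cure it only by contradicting the published text.

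**Working it through.** **1. The plan's own sample size.** Inputs from Sample size calculation: 60% vs 30%, two-sided α 0.05, power 80%.
- Unpooled variance: (1.96 + 0.842)² × (0.6×0.4 + 0.3×0.7) / 0.3² = 39.24, so 40 per arm. This matches the plan.
- Pooled variance: 41.97, so 42 per arm. At 40 per arm it gives 78.0% power.
- 40 × 1.1 = 44 per arm, 88 in total.

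The sample size does not depend on the adjustment rule and is not disputed here. It leaves little spare power.

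**2. How often the trigger fires.** Each true-null test fires with probability 0.05. With k independent tests, at least one fires with probability 1 − 0.95^k: 26% for k = 6, 34% for k = 8, 40% for k = 10. The article does not give k, and independence is an assumption.

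**3. Continuous outcomes.** Assumptions: 40 per arm, equal SD of 1 at baseline and end, true effect 0.6, baseline-final correlation r of 0.3, 0.5 or 0.7. The documents give no r. The variance of the estimated effect is (2/40) × V:
- change score: V = 2(1 − r)
- final score: V = 1
- ANCOVA: V = 1 − r²

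ANCOVA therefore has (1 − r²)/(2(1 − r)) = (1 + r)/2 of the change-score variance: 0.65, 0.75, 0.85.

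Approximate power is Φ(0.6/SE − 1.99):

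| r | SE change | SE final | SE ANCOVA | Power change | Power final | Power ANCOVA |
|---|---|---|---|---|---|---|
| 0.3 | 0.265 | 0.224 | 0.213 | 61% | 76% | 79% |
| 0.5 | 0.224 | 0.224 | 0.194 | 76% | 76% | 87% |
| 0.7 | 0.173 | 0.224 | 0.160 | 93% | 76% | 96% |

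Simulating the rule itself (ANCOVA only if the baseline t-test has P<0.05, 40,000 trials per setting):

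| r | Rule, change-score default | Rule, final-score default | ANCOVA always |
|---|---|---|---|
| 0.3 | 62% | 76% | 79% |
| 0.5 | 76% | 76% | 86% |
| 0.7 | 93% | 77 to 78% | 96% |

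**4. Type I error, continuous outcomes.** Overall, the rule rejects a true null in about 3.4 to 5.0% of trials. In the roughly 15% of null trials with a near-significant baseline difference (|t| from 1.28 to 1.99), the change-score test rejects in about 10%, 9% and 7 to 8%. ANCOVA stays near 5% there.

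**5. Binary primary.** Simulation with 40 per arm, 60% vs 30%, 3,000 trials per setting. The adjusted model has one baseline covariate plus site. The prognostic strengths are assumptions, because the documents give none.

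| Covariate log-odds per SD | Site shift (log-odds) | Rule | Adjusted always |
|---|---|---|---|
| 0 | 0 | 80% | 78% |
| 0.5 | ±0.5 | 81% | 82% |
| 1 | ±0.5 | 81% | 87% |
| 1 | ±1 | 81% | 89% |

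Under the null, in two of the prognostic settings, the rule rejected in 5.6% and 5.3% and the adjusted test in 6.3% and 5.7%. The Monte Carlo standard error is √(0.05×0.95/3000) = 0.4 points. A gain of one or two points should therefore not be leaned on.

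**6. Site stratification of the primary.** Chi-square against Cochran-Mantel-Haenszel, 44 per arm. With assumed site response rates of 35/45/55% the gain is about 1 point (for example 80.1% vs 80.9%). With 25/45/65% and allocation balanced by site it is 3 to 4 points (85% vs 88%, or 83% vs 87%, in separate runs). With no site effect there is none.

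**The case against.** **Baseline is not ignored.** A reader might infer that the recorded baseline values go unused. For continuous outcomes the documents do not support this, because efficacy is defined as a change from baseline. Subtraction does use the baseline, and at r = 0.7 the change-score loss is only about 3 points. This stands, and the concern is confined to how baseline is used.

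**False positives are not inflated overall.** A reader might infer from step 4 that the plan produces too many. It does not: the overall rate is at or below 5%. The excess arises only within the subset of trials with a moderate imbalance.

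**The large losses are not on the primary outcome.** This also stands. The variance ratio (1 + r)/2 has no counterpart for a responder status without a baseline value.

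**Site is a matter of silence.** The article neither includes nor excludes site, and a full protocol or analysis plan may add it. The section on randomization states no stratification by site. With a single unstratified list, the unadjusted chi-square has close to nominal type I error (4.7% at 25/45/65%) rather than the 3.4 to 3.8% seen when allocation is balanced by site. Site is therefore an optional gain and not a defect. A site main effect would also not answer the stated aim of comparing non-specific effects between Asian and Western patients.

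None of this defends the trigger, which is stated in the text and serves no purpose in a randomized comparison.

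**Conclusion.** The concern holds for the significance trigger, as a should-fix.

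- **Continuous secondary outcomes:** against pre-specified ANCOVA the rule gives up about 17, 10 and 3 points of power at r = 0.3, 0.5 and 0.7 if the default is the change score. If the default is the final score it gives up about 3, 10 and 18 points. These sizes rest on the assumed correlations and the 0.6 SD effect. The direction does not depend on which default is meant.
- **Binary primary:** the comparison remains valid and the sample size is untouched. The gain from adjustment runs from none to about 8 points under assumed prognostic strengths. What needs correcting is that the model, and with it the estimand, is left to a baseline test.

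Must-fix would be too strong: overall type I error is controlled, and the clear losses fall on secondary outcomes.

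**What to change.** 1. Delete the sentence that makes ANCOVA or logistic regression depend on a significant baseline difference. A baseline table may stay, but its P values should decide nothing.
2. For VAS, NDI, SF-36, STAI, PRISM and maximum tolerable volume, pre-specify ANCOVA of the v8 value on arm and the v1 value of the same measure. Do not use CARE or IRI at v1 in this way, since Table 3 places them after the first treatment.
3. Fix one primary comparison of responder proportions and its effect measure in advance, independent of any baseline test. Stratification by site (Cochran-Mantel-Haenszel, or logistic regression with site) is preferable but optional.

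The cost is a change of wording before unblinding: no new data and no extra patients. It uses one degree of freedom for the baseline value and two more if site is included.
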